### Study setting

This study will be conducted at Chung-Ang University Hospital in Seoul, Republic of Korea, in accordance with the principles of Good Clinical Practice and the Declaration of Helsinki.

### Eligibility criteria

The inclusion criteria are as follows:

1 Patients clinically diagnosed with idiopathic PD according to the UK Parkinson’s Disease Society Brain Bank Diagnostic Criteria (35).2 Patients classified as modified Hoehn and Yahr Stage 2–3.3 Patients who have provided informed consent and voluntarily signed the written consent form to participate in the study.

The exclusion criteria are as follows:

1 Patients with cognitive impairment [Mini-Mental State Examination (MMSE) score <24].2 Patients with musculoskeletal disorders that impair independent walking.3 Patients with limb amputation.4 Patients with medical conditions that affect the performance of activities of daily living.5 Patients with vestibular disorders or a history of vertigo.6 Patients deemed inappropriate for participation in the study by the investigator.

### Interventions

The participants will receive a 45-min rehabilitation exercise intervention session consisting of 20-min of strength training, a 5-min rest period, and 20-min of treadmill walking. Strength training will be conducted in a one-on-one setting with a skilled physical therapist and included hamstring and quadriceps stretching, one-leg bridging, hip abductor strengthening, quadriceps strengthening, bird-dog exercises, squatting, and one-leg standing exercises. During the treadmill walking session, participants were secured with a harness to ensure safety and walked at an individually self-selected speed within target of a moderate intensity range (Borg Rating of Perceived Exertion scale, RPE 11–13). The rehabilitation exercise program will be applied identically to all participants. The only difference between the two groups will be whether participants wear the soft wearable robot suit during the 20-min treadmill walking session. The intervention will be conducted 2 times per week, a total of 12 sessions for 6 weeks. We will review each participant’s medication schedule to determine their PD medication on/off periods. The intervention will be conducted during the “on” periods for each participant.

The intervention utilized the H-Medi (HUROTICS, Inc.), a cable-driven soft wearable robot suit designed for gait assistance (Figure 1). The system consists of a main module housing two motors and a battery, connected to a waist belt and a pair of thigh straps, with a total weight of 4.5 kg. Multiple apparel sizes were available to ensure a proper fit for each participant. Three IMU sensors, placed on the abdomen and both thighs, monitored the wearer’s movements in real time. The assistive force is generated by motors in the back-worn main module, a placement that positions the actuators near the body’s center of mass and minimize inertial burden. This force is transmitted to the thighs via a flexible Bowden cable system. The waist belt serves as the proximal anchor, while the distal end of the cable connects to an attachment point on the thigh strap. This provides targeted assistance, enabling the force to be precisely applied to desired muscle groups without interfering with the user’s natural movements. In this study, the H-Medi was configured to assist hip extension with the goal of enhancing forward propulsion and gait stability, thereby increasing gait speed in patients with PD. Although the device can deliver a maximum assistive force of 200 N (≈ 30 Nm), the experimental range was set between 30 N (≈ 4.5 Nm) and 130 N (≈ 19.5 Nm). Force magnitude was adjusted by the physical therapist based on clinical judgment and was progressively increased from 30 N throughout training. This clinical judgment was guided by a clinical judgment integrating the participant’s subjective feedback on exertion (Borg RPE scale), the therapist’s observation of gait stability without excessive compensatory movements, and a qualitative assessment of overall movement quality (e.g., observed changes in stride length, stability, and posture). Treadmill speed was concurrently raised to augment the rehabilitation effect, with both parameters modulated according to each participant’s self-selected walking speed and Borg RPE scale. The assistive force profile followed a half-sine waveform defined by three key gait timings from prior optimization studies in healthy adults: onset at approximately 13% of the gait cycle before heel strike, peak at 21% after heel strike, and offset at 38% after heel strike (36). The gait cycle was estimated based on hip-centric events, such as Maximum Hip Extension (MHE) and Maximum Hip Flexion (MHF), detected by the IMU sensors on the abdomen and thighs. This profile was further individualized based on participant feedback and the therapist’s expertise to ensure optimal assistance.

**Figure 1 fig1:**
[figure not shown]
The cable-driven soft wearable robot suit (H-Medi), showing key components such as including main unit (black boxes), sensors (yellow boxes), straps (green boxes), and directions of applied forces (red boxes).

The criteria for discontinuing the intervention are as follows:

1 Voluntary withdrawal by the participant.2 Missing a total of 3 out of 12 intervention sessions.3 Consecutively missing 2 intervention sessions.4 Discontinuation due to significant adverse events.5 Research investigator’s judgment that the continuation of the intervention is unsuitable.

The rehabilitation exercise session has been established as effective for patients with PD, regardless of the use of the soft wearable robot. Therefore, participants will be informed that assignment to either study group may not adversely affect their physical impairments or functional levels during the intervention period. Additionally, since all interventions will take place within the hospital, research coordinators will maintain periodic contact with participants via phone calls to remind them of upcoming interventions.

Participants will maintain their usual dosage of medication for their underlying conditions, including PD. Beyond the exercise intervention implemented in this study, any additional physical activities conducted at medical centers, including rehabilitation centers, are prohibited.

### Outcomes

Baseline evaluations (T0) will be conducted within 7 days before the initiation of the intervention. Post-intervention evaluations (T1) will be conducted within 7 days after the final intervention session.

The primary outcome will be the change in gait speed from T0 to T1. Gait speed will be measured as the average value from two trials of the 10-meter walk test. This test is sensitive to mobility impairment, predicts disability and falls, and is feasible for use in clinical settings, demonstrating both reliability and validity (37, 38).

The secondary outcomes will be the change from T0 to T1 of the following assessments: 4-meter walk test, TUG, Short Physical Performance Battery (SPPB), BBS, MDS-UPDRS, Freezing of Gait Questionnaire (FoGQ), gait parameters measured by an IMU sensor-based gait analysis system (Human Track, R. Biotech Co. Ltd., Seoul, Korea) (39) and the GAITRITE system (CIR Systems, PA, United States) (40), muscle strength and endurance measured by isokinetic dynamometer Biodex system (Biodex System 4, Biodex Medical Systems, Shirley, NY, United States) (41), thickness of quadriceps muscles measured by ultrasound, body composition measured by Dual-energy X-ray absorptiometry (DEXA) (42), cognitive function measured by Mini-Mental State Examination (MMSE), and depression measured by Beck Depression Inventory (BDI). In addition, questionnaires assessing comfort and usability, along with participants’ feedback, will be collected after the completion of the intervention sessions.

The TUG evaluates gait, balance, and fall risk. Participants will rise from a chair, walk 3 meters to a cone, turn, return to the chair, and sit down. Completion time (seconds) will be recorded (43). The SPPB will assess balance, walking ability, and transfers. Each component is scored on a 0–4 scale, with a total score ranging from 0 to 12, where higher scores indicate better performance. The BBS assesses functional standing balance through 14 tasks of increasing difficulty, including sitting, standing, single-leg stance, and positional changes. Each item is scored on a 0–4 scale, with a maximum total score of 56, where higher scores indicate better balance ability (44).

The MDS-UPDRS is a comprehensive tool for evaluating Parkinson’s disease across four domains: (I) non-motor experiences of daily living, (II) motor experiences of daily living, (III) motor examination, and (IV) motor complications. Parts I and II are based on patient or caregiver questionnaires, while Parts III and IV are assessed by a clinician. Each item is rated on a 0–4 scale, with higher scores indicating greater impairment, allowing for a detailed assessment of both motor and non-motor symptoms (45). The FoGQ is a brief, reliable self-reported instrument designed to assess FoG in individuals with Parkinson’s disease. It consists of six items evaluating the frequency, duration, and impact of FoG episodes, such as start hesitation and turning hesitation. Each item is scored on a 0–4 scale, with higher scores indicating more severe symptoms (46).

The gait parameters measured by the IMU sensor-based gait analysis system and the GAIRRite system will include stride length, step length, cadence, proportion of single and double support, proportion of swing and stance phases, and the range of motion (ROM) of hip, knee, and ankle joint angles. The parameters measured by the Biodex system will include the number of repetitions, peak torque (N·m), peak torque/body weight (%), maximal repetition total work (J), coefficient of variation (CV, %), average power (W), and total work (J). Measurement will be obtained for both knee flexion and extension at angular velocities of 60°/second and 180°/second.

Quadriceps muscle thickness will be measured by ultrasound. A single trained investigator will perform all measurements. The probe will be placed transversely, 10 cm above the superior border of the patella, along the line from the anterior superior iliac spine to the patella (47, 48). Body composition will be assessed using DEXA, including measurements of body mass index (BMI), skeletal muscle mass index (SMI), total body fat percentage, fat mass index, and bone mineral density (BMD).

Cognitive function and mood are often impaired patients with PD (49). Additionally, exercise may have a positive effect on these dysfunctions (50–52). Therefore, we included cognitive and depression as secondary outcomes. Cognitive function will be assessed using the MMSE, a widely used screening tool for global cognitive status that is sensitive to cognitive decline in patients with Parkinson’s disease (53). Depression will be evaluated using the BDI, a validated self-report questionnaire that reliably measures the severity of depressive symptoms in this population (54). Both tools have been extensively used in PD research and are practical for clinical and research settings.

### Participant timeline

Figure 2 shows the brief design and flowchart of the study. All participants will be enrolled in the study after completing the predefined screening process. Following enrollment, baseline evaluations will be conducted. Within 7 days of these evaluations, the rehabilitation exercise intervention will begin, consisting of 12 sessions over 6 weeks. After the intervention, post-intervention evaluations will be conducted within 7 days. The specific timeline of participants is shown in Table 1.

**Figure 2 fig2:**
[figure not shown]
Design and flowchart of the study.

**Table 1 tab1:** Timeline of enrollment, interventions, and assessments of the study.

Time point	Enrollment	Baseline (T0)	Intervention	Post-intervention (T2)
Informed consent	O			
Eligibility screen	O			
Group assignment		O		
Assessments				
Gait speed		O		O
TUG		O		O
SPPB		O		O
BBS		O		O
MDS-UPDRS		O		O
FoGQ		O		O
Gait parameters		O		O
Muscle strength and endurance		O		O
Quadriceps thickness		O		O
Body composition		O		O
MMSE		O		O
BDI		O		O
Safety analysis		O		O
Application of intervention				
Intervention			O	

TUG, Timed-Up and Go test; SPPB, Short Physical Performance Battery; BBS, Berg Balance Scale; MDS-UPDRS, Movement Disorder Society-Unified Parkinson’s Disease Rating Scale; FoGQ, Freezing of Gait Questionnaire; MMSE, Mini-Mental State Examination; BDI, Beck Depression Inventory.

### Sample size

The primary outcome of this study is the change in gait speed between T0 and T1, which has been widely used in previous studies (9). The power of the study (1–*β*) was set at 80%, with a significance level (*α*) of 5%. The required sample size was calculated using Lehr’s formula (55). The clinically significant effect size (*δ*) was been designated as 0.18, with an expected standard deviation (*σ*) of 0.17 (22, 38). Considering an anticipated follow-up rate of 80%, the final calculated sample size was 17 participants per each group, totaling 34 participants.

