## Methods

### Trial design

This is a prospective, single-center, single-blind, parallel-group trial. Participants will be assigned to two groups, in a 1:1 ratio: the robot group and the control group. The intervention session times will be pre-assigned as either robot or control sessions, with an equal number of slots for each group. Participants will then select their preferred session time according to their personal schedules, without knowing which sessions are designated as robot or control. Their group allocation will be determined based on this selection. As randomization is not employed and group assignment is based on self-selection, potential selection bias and confounding may occur. However, since session times for both groups are evenly distributed and baseline demographic and clinical characteristics of participants will be collected, we suggest that potential bias can be minimized. In the analysis of study results, we will apply appropriate statistical adjustments for any baseline differences. One research investigator will manage the session schedule and contact participants. This investigator, physical therapists conducting the intervention, and the participants will not be blinded to group assignments. All other investigators including outcome assessors, investigators involved in data interpretation and analyses, and the principal investigator (PI) will remain blinded throughout the study. Group assignments will be unblinded only after completion of the final statistical analyses, or during the study if a serious adverse event occurs, with the approval of the PI.

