### Statistical methods

Demographic and clinical characteristics will be summarized using frequencies and percentages for categorical variables and means with standard deviations (SD) for continuous variables. The Shapiro–Wilk test will be used to assess the normality of continuous variables. To compare baseline characteristics between the intervention and control groups, an independent t-test will be applied for normally distributed variables, while the Mann–Whitney U test will be used for non-normally distributed variables.

All participants who undergo the intervention will be included in the intention-to-treat (ITT) population, which will also serve as the basis for safety analyses. Participants in the ITT population who complete both baseline and post-intervention assessments will comprise the full analysis set (FAS). Efficacy analyses will be conducted based on the FAS.

For efficacy analyses, the normality of outcome variables will be assessed using the Shapiro–Wilk test. Baseline characteristics will be included as covariates for adjustment in the statistical models. Additionally, comparisons between the robot (intervention) and control groups under each condition will be performed using either the independent t-test or the Mann–Whitney U test, depending on the distribution of the data. To compare post-intervention outcomes between the groups while adjusting for baseline values, analysis of covariance (ANCOVA) will be used. The post-intervention measurement will be the dependent variable, group assignment the independent factor, and the baseline measurement of the outcome will be included as a covariate. This approach accounts for any baseline imbalances and increases statistical power. Assumptions of normality and homogeneity of regression slopes will be assessed prior to analysis. Statistical significance will be set at a two-sided *p*-value of <0.05 for all analyses.

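### Seventeen per group does not follow from the article's own sample-size inputs, which give 18; the effect on power is small

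*Protocol article*

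**What the plan says.** The Sample size section of the protocol article names change in gait speed as the primary outcome and Lehr's formula as the method. Power "was set at 80%, with a significance level" of 5%. The difference to detect "was been designated as 0.18, with an expected standard deviation" of 0.17. No unit is printed for either figure, and the text does not say whether 0.17 describes change in speed or speed at one visit. The section ends: "Considering an anticipated follow-up rate of 80%, the final calculated sample size was 17 participants per each group, totaling 34 participants". It shows neither the number needed before allowing for losses nor a rounding rule.

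Three statements elsewhere bear on the calculation:

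- Trial design: "Participants will be assigned to two groups, in a 1:1 ratio".
- Statistical methods, on testing: "Statistical significance will be set at a two-sided" p-value below 0.05.
- Statistical methods, on the analysis set: the full analysis set (FAS) holds participants who have both the baseline and the post-intervention assessment, and "Efficacy analyses will be conducted based on the FAS".

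The same section lists an independent t-test (or Mann–Whitney U test) between groups and an analysis of covariance (ANCOVA) of the post-intervention value with the baseline value as covariate.

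**The concern.** The article prints every input that Lehr's formula needs, so a reader can repeat the calculation, and it does not return 17. The allowance for losses is meant to leave enough completers to meet the formula's requirement. Because efficacy is analysed in completers only, each participant lost reduces the number analysed. If 17 enrolled leave fewer than the formula asks for, the 80% power is slightly overstated under the article's own assumptions. In a trial of 34, a result that misses significance will be read against the stated power, so that figure should be one the inputs support.

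**Working it through.** **Inputs.** Difference δ = 0.18, standard deviation σ = 0.17, power 80%, α = 5% and follow-up 80% (Sample size); two-sided testing (Statistical methods); 1:1 allocation (Trial design). The standardised difference is 0.18/0.17 = 1.059.

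**Step 1: completers needed.**
- Lehr's formula, n = 16 × (σ/δ)² = 16 × 0.8920 = 14.27 per group.
- The normal approximation that Lehr rounds, n = 2 × (1.960 + 0.842)² × (σ/δ)² = 15.70 × 0.8920 = 14.00 per group.

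**Step 2: allow for losses by dividing by 0.8.**

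| Completers per group | ÷ 0.8 | Enrol per group | Total |
|---|---|---|---|
| 14.27 (rounded up once, at the end) | 17.84 | 18 | 36 |
| 14 | 17.50 | 18 | 36 |
| 15 (14.27 rounded up first) | 18.75 | 19 | 38 |

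**Step 3: try to reproduce 17.** Rounding 17.84 or 17.5 down gives 17. So does multiplying 14 by 1.2 (16.8, rounded up), or 14.27 by 1.2 (17.13, rounded to the nearest whole number). A one-sided test gives 12 and then 15, so it is not the explanation. The article does not show which route was taken. None of those that reach 17 is division by 0.8 with upward rounding.

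**Step 4: check in reverse.** 17 × 0.8 = 13.6 expected completers per group, below both 14.00 and 14.27.

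**Step 5: power for a difference of 0.18, two-sided 5%.** The t-test column uses the noncentral t distribution.

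| Completers per group | Normal approximation | Unadjusted t-test |
|---|---|---|
| 13 | 77.0% | 73.6% |
| 13.6 (17 enrolled) | 78.8% | 75.6% |
| 14 | 80.0% | 76.9% |
| 14.4 (18 enrolled) | 81.1% | 78.2% |
| 15 | 82.6% | 79.9% |
| 17 (no losses) | 87.0% | 84.9% |

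At 13.6 per group, the difference detectable with 80% power is 0.183 by the normal approximation and 0.190 by the t-test.

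**Step 6: split the t-test shortfall.** From 80% down to 75.6% is 4.4 points. Enrolling 18 would still give 78.2%, so 1.8 points are due to Lehr's approximation being slightly optimistic at this size. The other 78.2 − 75.6 = 2.6 points are due to enrolling 17 and not 18.

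**Step 7: the planned ANCOVA.** This step assumes that 0.17 is the standard deviation of change and that the variance is equal at both visits. With baseline-to-post correlation r, the residual standard deviation is 0.17 × √((1 + r)/2). At 13.6 per group:

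| Assumed r | Residual SD | Power |
|---|---|---|
| 0.7 | 0.157 | about 82% |
| 0.8 | 0.161 | about 80% |
| 0.9 | 0.166 | about 78% |

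The article gives no correlation, so these values of r are assumptions.

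**The case against.** The strongest defence is that this is one participant per group. Lehr's 16 is itself a rounded-up constant, and the unrounded approximation needs 14.00. On that basis, which is the article's own method, power at 13.6 completers is 78.8%, only 1.2 points below the stated figure. The 75.6% comes from a t-test calculation that the Sample size section did not use. The planned ANCOVA may also recover the loss: the Statistical methods section says that adjustment raises power, and lower correlations than those tabulated would give more than 82%.

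Most of this stands and limits the size of the point. It does not make 17 the result of the stated inputs. The ANCOVA argument is also conditional, because the Sample size section neither invokes ANCOVA nor gives a correlation, and does not say what 0.17 measures.

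A reader might infer three stronger things that the article does not support:

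- **That the authors multiplied by 1.2 when they should have divided by 0.8.** This is possible, but simple rounding down gives the same 17 and the article shows no working.
- **That 19 per group is the only correct answer.** It follows only from rounding up at both steps; rounding once gives 18.
- **That self-chosen session times will leave unequal groups and so lower power further.** The article states a 1:1 ratio with equal numbers of slots, and gives no figure for any imbalance.

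**Conclusion.** The point holds as a small arithmetic slip. The stated inputs give at least 18 per group (36 in total), not 17 (34). With 17 enrolled and 80% followed up, 13.6 per group are expected in the FAS, against 14.27 required.

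Power for 0.18 is then about 79% on the basis of Lehr's formula, or about 76% by an unadjusted t-test, which reaches 80% at a difference of about 0.19. Only part of the t-test gap is caused by the slip. These figures take 0.17 as the standard deviation of the quantity compared, equal losses in the two groups, and exactly 80% follow-up.

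A reader might conclude that the trial is materially underpowered, or that its power is 76% without qualification. The article supports neither: the shortfall on its own method is 1.2 points, and the planned ANCOVA could give about 78% to 82% under the assumptions in the working. The division is certain. The cause of the slip, and the power of the adjusted analysis, cannot be settled from the article.

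**What to change.** Reword the Sample size paragraph:

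- Show the number needed before losses (14.27 per group) and state the rounding rule.
- Correct the inflated figure to 18 per group (36 in total), or 19 (38) if the rule is to round up at both steps.
- If 34 remains the planned number, say so beside the corrected figure and restate its power for 0.18 at 80% follow-up: about 79% by the normal approximation, or about 76% by the t-test.
- Alternatively, base the power on the planned ANCOVA and state the baseline-to-post correlation assumed, with its source.
- In either case, give the unit of 0.18 and 0.17 and say whether 0.17 is the standard deviation of change.

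The cost is one paragraph and a slightly less favourable stated power. No extra patients are needed, and the design, primary outcome and analysis do not change.
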